A promising intervention is systemic vibratory therapy (SVT), which uses vibration platforms to provide mechanical stimuli capable of eliciting muscular, proprioceptive, and hormonal responses [12,13]. Reduced muscle strength, impaired sensory integration, and altered postural adjustments in older adults are associated with an increased risk of falls [11]. Previous studies suggest that SVT may improve lower limb muscle performance, balance, mobility, and physical function in older populations, although the magnitude of these effects appears to depend on protocol characteristics such as frequency (F), peak-to-peak displacement (D), exposure time, rest intervals, and body position during vibration exposure [13,14]. Despite these potential benefits, the ideal SVT protocol for older adults is not yet defined. Current evidence still shows considerable heterogeneity regarding vibration parameters, intervention duration, equipment characteristics, and participant positioning, which limits the establishment of standardized recommendations for clinical practice [12]. Body position during SVT can be particularly relevant, as it can modify axial load, lower limb muscle activation, postural demand, comfort, and safety. The semi-squat position can increase active lower limb engagement and proprioceptive stimulation, while the seated position can reduce weight-bearing demands and provide a more tolerable alternative for frail, sedentary, or low-functional older adults [13,14,15]. Therefore, comparing these positions can help clarify whether the effects of SVT are primarily related to exposure to mechanical vibration itself or to the combination of vibration with active postural and muscular demands.

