Beyond objective fall risk metrics, concern about falling is a patient-centered outcome that can constrain activity participation and undermine adherence to exercise-based prevention strategies. Conceptually, falls efficacy reflects an older adult’s perceived capability to prevent and manage falls in daily life; thus, quantifying change in this construct provides clinically relevant information that complements performance- and physiology-based outcomes [16,17]. The Falls Efficacy Scale-International (FES-I) is among the most widely used instruments to assess concerns about falling, and recent syntheses support its measurement properties and interpretability for older populations, although responsiveness benchmarks may vary across settings [18]. Accordingly, the present trial defines change in FES-I from baseline to post-intervention as the primary endpoint, while physical conditioning, neuromuscular activity, and postural control outcomes are retained as secondary measures to help contextualize potential physiological pathways of systemic vibratory therapy combined with habitual physical activity. Thus, this study aims to compare the effects of SVT associated with a physical activity program on fall concern in older adults. As secondary outcomes, the study will assess functional physical fitness, electromyographic activity, muscle synergy, and center of pressure oscillation [12,13,14,15].

Our hypothesis is that SVT combined with habitual physical activity will produce greater improvements in concern about falling, functional fitness, postural control, and neuromuscular variables compared with habitual physical activity alone. We also hypothesize that the semi-squat and seated SVT positions may produce different neuromuscular responses due to differences in axial load, lower limb muscle activation, and postural demand.

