### 2.11. Concern About Falling

Concern about falling will be assessed using the Falls Efficacy Scale-International, Brazilian version (FES-I-Brazil). This questionnaire presents questions about the perception of fear of falling when performing 16 activities. Each activity has a score from one to four, with 1 point (not at all concerned), 2 points (slightly concerned), 3 points (moderately concerned), and 4 points (extremely concerned). The total score can range from 16 to 19 points (low concern), 20 to 27 points (moderate concern), and 28 to 64 points (high concern). This instrument will be administered at baseline and within 48 h after the final intervention session [16,17,18]. In addition to analyzing FES-I as a continuous outcome within the planned Group × Time framework, interpretability will be supported by reporting the proportion of participants who shift across established concern categories (low/moderate/high) from baseline to post-intervention. Because MCID/MID thresholds for patient-reported outcomes can vary substantially across estimation methods and populations, and because credible anchor-based MIDs are not consistently available for community-dwelling older adults, the study will also apply a transparent distribution-based benchmark (0.5 baseline SD) to describe a minimal important change in FES-I as a supplementary interpretive reference rather than a substitute for the primary inferential model [23,24]. This approach is intended to strengthen clinical interpretability while avoiding overstatement of “clinical significance” in the absence of stable, population-specific anchor-based thresholds.

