### 2.16. Statistical Analysis

Sample size calculation

An a priori sample size calculation was performed using G*Power software (v. 3.1.9.6) [28]. A conservative medium omnibus effect size (Cohen’s f = 0.25) was adopted, consistent with methodological guidance for a priori estimation in strength and conditioning/exercise research [29]. Assuming α = 0.05, power (1 − β) = 0.80, and three parallel groups, the required total sample size for an omnibus ANOVA comparison is 159 participants (53 per group). To account for potential losses to follow-up of up to 20%, the planned recruitment target was increased to 192 participants (64 per group), ensuring adequate power for the primary analyses. Participants of both sexes, over 60 years of age (M01.060.116.100), participating in the Open University for the Elderly program at Augusto Motta University (UNATI/UNISUAM), will be included.

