### 2.17. Data Analysis

Descriptive statistics will be presented as mean ± standard deviation for continuous variables and as frequency (percentage) for categorical variables. Distributional assumptions will be evaluated using Shapiro–Wilk tests and visual inspection (histograms and Q–Q plots), and homogeneity of variance will be examined (e.g., Bartlett/Levene, as appropriate). Because the trial includes three groups and two time points (baseline and post-intervention), the primary inferential objective for each outcome will be to test the Group × Time interaction, which directly evaluates whether pre–post changes differ between groups.

For outcomes meeting parametric assumptions, a mixed-design model will be applied with Group (A, B, C) as a between-subject factor and Time (baseline, post-intervention) as a within-subject factor. The main effect of Group, main effect of Time, and, critically, the Group × Time interaction will be reported. Because Time has only two levels, sphericity is not applicable. If the interaction is statistically significant, planned follow-up comparisons (simple effects) will be conducted to compare: (i) pre–post change within each group and/or (ii) between-group differences at each time point, using multiplicity-adjusted procedures (see below).

If parametric assumptions are violated, outcomes will be analyzed using an appropriate robust repeated-measures approach (e.g., transformation where suitable, or mixed-model estimation with robust standard errors), preserving the Group × Time framework. In all cases, inference will be centered on the interaction term as the test consistent with the study design.

Multiplicity control: The primary outcome (FES-I) will be tested at α = 0.05 (two-sided). Secondary outcomes will be interpreted as supportive/exploratory and will include multiplicity control to reduce false-positive risk across the outcome family. For post hoc/simple-effects contrasts following a significant interaction, *p*-values will be adjusted (e.g., Holm–Bonferroni). For multiple secondary outcomes, an additional correction strategy will be applied (e.g., false discovery rate control) to maintain interpretability across the secondary endpoint set.

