According to Meirelles et al. [36] in their systematic review, they demonstrated that there are positive effects in the use of SVT in relation to the risk of falls in the elderly, but they highlight the lack of standardization of a well-established protocol. Yang and Butler [37] concluded in a meta-analysis that SVT may benefit mobility and balance immediately, but its effect may not persist among people with stroke, suggesting that more studies with high methodological quality are needed to determine the cumulative effects of SVT in this population.

Similarly, Kocic et al. [33] added physical exercise to the usual care in nursing home residents over 65 years of age for 6 months and found a significant improvement in the time to perform on the Timed Up and Go (TUG) test, the Five Times Sit-to-Stand Test (FTSTS), and FIM scores. Furthermore, it was observed that the changes in the TUG and FTSTS test values were significantly different between the groups, as well as for the Functional Independence Measure (FIM), with better values in the EVCI group, while in the usual care group the values worsened; however, there is no evaluation of different positions during the use of SVT [34].

The comparison between semi-squatting and seated positions during the SVT is clinically relevant, since these positions may produce different neuromuscular and systemic demands [12,13,15]. In the semi-squatting position, participants are exposed to a greater axial load and greater activation of the lower limb muscles, which can increase proprioceptive stimulation and activation of the muscles involved in postural control [13,31]. In contrast, the seated position may reduce the weight-bearing demand and offer a safer and more tolerable alternative for older adults with lower functional capacity or concern about falling, since SVT may generate both local and systemic effects [14,15,20]. Furthermore, this postural strategy during SVT has been studied, but still lacks a well-defined protocol, as well as a comparison with the use of SVT in other postures in older adults [12,25,30]. Therefore, comparing these two positions can help clarify whether the therapeutic effects of SVT are mainly related to exposure to mechanical vibration alone or to the combination of vibration with active postural and muscular demands.

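### The semi-squat versus seated difference in FES-I change is not a named contrast, and no contrast between the positions is run after a null omnibus test, so a null result cannot support the reading that vibration itself drives the effect

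*Protocol article*

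**What the plan says.** The Introduction gives the reason for having two vibration arms: "comparing these positions can help clarify whether the effects of SVT are primarily related to exposure to mechanical vibration itself", as against vibration combined with active postural and muscular work. The Discussion repeats it: "comparing these two positions can help clarify whether the therapeutic effects of SVT are mainly related to exposure to mechanical vibration alone". The only hypothesis about position, in the Introduction, is one of difference and concerns neuromuscular variables: "the semi-squat and seated SVT positions may produce different neuromuscular responses".

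Section 2.17 centres inference on the Group × Time interaction across the three groups. Follow-up is conditional: "If the interaction is statistically significant, planned follow-up comparisons (simple effects) will be conducted to compare" (i) pre-post change within each group and/or (ii) differences between groups at each time point. These p-values are adjusted, with Holm-Bonferroni as the example. No confidence-interval rule is given for semi-squat versus seated.

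Section 2.16 sizes the trial on the omnibus test alone: "A conservative medium omnibus effect size" of f = 0.25, three groups, alpha 0.05 and power 0.80, giving 159 participants, raised to 192 for losses of up to 20%. Section 2.11 will "apply a transparent distribution-based benchmark (0.5 baseline SD) to describe a minimal important change in FES-I", as a supplementary aid to interpretation.

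**The concern.** The question in the Introduction and Discussion has two possible answers. If semi-squat does better than seated, postural demand adds something. If the effect is mainly due to vibration itself, the difference between the positions should be small. The first answer can come from a significance test. The second needs a bound on the difference, meaning an estimate with an interval.

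The analysis in section 2.17 supplies no such estimate. Within-group changes do not compare the positions. Differences at each time point are not the difference in change. Neither is reached when the three-group interaction is non-significant. In that case the article's own question about position is left with no contrast at all. When the gate is open, a null result is only an adjusted p-value above 0.05.

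At stake is how a null result is read. The Discussion describes the seated position as possibly safer and more tolerable, so a conclusion that position makes no difference would carry practical weight.

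**Working it through.** **Inputs.** From section 2.16: f = 0.25, alpha 0.05, power 0.80, 53 per group before losses, 64 per group recruited. A 20% loss leaves 192 × 0.8 = 153.6, about 51 per group. From section 2.17: omnibus gate, then Holm. Assumed: a true semi-squat minus seated difference of 0.5 SD on the analysed scale, and normal data.

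**The plan's own figure.** With two time points, the Group × Time test is a one-way ANOVA on change scores. The noncentrality is N·f² = 159 × 0.0625 = 9.94 with 2 and 156 degrees of freedom, which gives power 0.805. The smallest N is 158, or 159 with equal groups, so 159 is reproduced. It says nothing about any one pair.

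**Two-arm test alone, no gate or adjustment.** Noncentrality is d·√(n/2):
- n = 64: 0.5 × √32 = 2.83, power 0.801, missed 20%
- n = 53: 0.5 × √26.5 = 2.57, power 0.722, missed 28%
- n = 51: 0.5 × √25.5 = 2.52, power 0.706, missed 29%

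This is a reference only, since section 2.17 plans adjusted p-values.

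**Gate plus Holm over three pairs (simulation, unit SD).** The position difference is 0.5 SD in every row; the control mean is 0. The columns give percentages at 64 / 53 / 51 per arm.

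| Semi-squat, seated | Gate closed, positions not compared | Difference missed in total |
|---|---|---|
| 0.25, −0.25 | 29 / 38 / 40 | 34 / 43 / 45 |
| 0.5, 0 | 17 / 25 / 26 | 31 / 41 / 43 |
| 0.75, 0.25 | 2 / 5 / 6 | 26 / 36 / 38 |
| 1.0, 0.5 | under 1 | 21 / 30 / 32 |

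The overall range is about 21-45%.

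**Dependence on the pre-post correlation r.** If 0.5 is in baseline SDs and the test is on change scores, the SD of change is √(2(1 − r)) baseline SDs, so the standardised difference is 0.5/√(2(1 − r)). At r = 0.5 this is 0.5. The article gives no r. Between an unadjusted test at 64 per arm and a Bonferroni test (0.05/3) at 51 per arm, the miss rate is:
- r = 0.3: 34-61%
- r = 0.5: 20-46%
- r = 0.7: 5-21%
- r = 0.8: 1-6%

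**Precision.** The 95% interval for semi-squat minus seated has half-width t·√(2/n): 0.35 SD at 64 per arm, 0.39 SD at 53 and at 51. A null result would therefore often be compatible with differences of a few tenths of an SD in either direction.

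**Would 0.5 SD serve as a similarity margin?** The largest spread of three means consistent with f = 0.25 lies between 0.25 × 6/√8 = 0.53 SD and 0.25 × √6 = 0.61 SD, so a 0.5 SD margin is nearly the whole effect the trial is sized for. Take control 0, seated 0.25 and semi-squat 0.5 SD, so that half the effect depends on position. A rule that the 90% interval must lie within ±0.5 SD needs the estimate within ±(0.5 − 0.293) = ±0.207 at 64 per arm, or ±(0.5 − 0.329) = ±0.171 at 51. With a true difference of 0.25 and standard errors of 0.177 and 0.198, that happens in about 40% and 33% of trials. The rule would too often call the positions similar.

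**The case against.** The strongest reply is that the article contains no faulty decision rule. It says only that the comparison can help clarify a question, in background and discussion text. Its one hypothesis on position is a difference hypothesis about neuromuscular variables, for which a difference test is suitable. That is right. A reader might infer that the authors will take p > 0.05 as showing that position does not matter; nothing in the article says so. A reader might also infer that the vibration-itself answer can come only from a null comparison of the positions. That too is overstated: seated versus control shows whether vibration without the squat has any effect. It cannot show that vibration is the main cause unless the difference between positions is bounded.

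Second, the miss rate rests on an unstated correlation and could be very small. This also stands, and the range is shown for that reason. The main argument does not need the figure: non-significance does not establish similarity at any correlation.

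Third, reporting of intervals is commonly left to the analysis plan, which is not shown. This has some force, and the absence of a margin is not held against the article. But section 2.17 does fix a specific conditional rule with listed contrasts, and that rule does not deliver the comparison which the Introduction and Discussion rely on.

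**Conclusion.** The point holds as a mismatch between the stated use of the position comparison and the analysis in section 2.17. The semi-squat minus seated difference in FES-I change is not named, and no contrast between the positions is run after a null omnibus test. A null or untested contrast therefore cannot support attributing the effect to vibration itself.

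For a true 0.5 SD difference the planned procedure misses about 21-45% of the time with 64 to 51 per arm. This assumes that the gate and the contrasts are tested on the same scale, that Holm covers three pairs and, for change scores, that the pre-post correlation is 0.5. The rate falls to about 1-6% at 0.8 and rises at lower correlations.

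Two stronger readings are not supported. The 0.5 baseline SD in section 2.11 is a supplementary reference for change in FES-I, not a margin between positions. And even close agreement between the two arms would not isolate vibration: the Discussion acknowledges that, without a sham, device contact, time and laboratory exposure are not fully controlled. The primary omnibus test is unaffected, so this is an inexpensive improvement and not a defect in the main inference.

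**What to change.** In section 2.17, make the semi-squat minus seated difference in FES-I change a planned contrast from the same model, always reported with its confidence interval whether or not the interaction is significant. Add one sentence stating that p > 0.05, or an untested contrast, is not evidence that the positions are similar.

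Soften the matching sentences in the Introduction and Discussion so that they speak of estimating the difference between positions, and do not suggest that a null result would identify vibration as the cause. If the sponsor wants a formal similarity claim, it should justify a margin separately and in advance, and check whether the sample size supports it.

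The cost is a few sentences and one interval, with no extra participants or measurements. The drawback is that a null result on position will often have to be reported as inconclusive.

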A total of 192 older adults enrolled in the Open University for the Elderly (UNATI) at Centro Universitário Augusto Motta (UNISUAM), Bonsucesso Unit, will be recruited. Participants will be allocated in a 1:1:1 ratio into three groups using sequentially numbered, opaque, sealed envelopes prepared from a computer-generated randomization list. The allocation sequence will be implemented after completion of baseline assessments to preserve allocation concealment. In the control group (Group A), participants will be considered a usual physical activity control group. Participants allocated to this group will continue their regular activities offered by the UNATI/UNISUAM program, including light walking, stretching exercises, activities of daily living, and recreational cognitive activities. No additional vibration stimulus or sham-vibration procedure will be applied. Therefore, the study will compare systemic vibratory therapy combined with habitual physical activity in two distinct positions versus habitual physical activity alone. In the semi-squat intervention group (Group B), participants will engage in the same routine activities and, 30 min after the end of their UNATI sessions, will be directed to the Laboratory of Musculoskeletal Performance of the Graduate Program in Rehabilitation Sciences (PPGCR/UNISUAM), where SVT will be performed in a semi-squat position with knees flexed at 120°. To ensure positioning consistency, the platform base will be pre-marked to standardize foot placement. The intervention will use mechanical vibration at F of 15, 20, and 25 Hz with a D of 5 mm, corresponding to peak accelerations (Apeak) of 2.3 g, 4.1 g, and 6.4 g. Each frequency will be applied for 1 min, with a 1 min rest interval between frequencies, in a cycle repeated three times, totaling 18 min per session. Interventions will occur twice weekly, for a total of 10 sessions. All sessions will be conducted by a research assistant trained in the operation of the vibration platform. Systemic vibratory therapy will be delivered using a Kikos P204IXC alternating oscillatory vibration platform (manufacturer is Kikos) manufactured in São Paulo, Brazil.

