### 2.9. Interventions

The protocol will be performed by a trained physiotherapist who is unaware of the initial assessment and will be conducted in accordance with the requirements of the Model for Description and Replication of Interventions TIDieR [22].

In the control condition, participants will continue their routine activities offered by the UNATI/UNISUAM program and will only undergo the scheduled clinical, sociodemographic, and outcome assessments. This group will be considered a usual physical activity control group, without additional vibration stimulus or sham-vibration procedures.

Semi-squat intervention group: Participants will perform their routine activities from the UNATI/UNISUAM program and SVT in a semi-squat position (knee flexion at 120°) using the following biomechanical parameters: F = 15, 20, and 25 Hz and D = 5 mm, Apeak of 2.3 g; 4.1 g and 6.4 g. The participant will perform 1 min of vibration in each D position (D = 5 mm) with 1 min of rest between each, repeating 3 times, totaling 18 min of intervention in a total of 10 interventions, twice a week. For standardization of the D position, the base of the vibration will be marked beforehand where participants should keep their feet during the sessions. SVT will be performed at least 30 min after their activities proposed by the UNATI/UNISUAM program.

Seated intervention group: Participants will perform the routine activities of the UNATI/UNISUAM and SVT programs while seated in a chair with their hands resting on their knees. The biomechanical parameters will be the same as those reported for the semi-squat position.

Adherence to the intervention will be monitored using individual attendance logs completed at each session by the research team. The number of completed sessions, missed sessions, and reasons for absence, when available, will be recorded. Adherence will be expressed as the percentage of completed sessions relative to the total number of planned sessions. Participants who complete at least 80% of the planned sessions will be considered adherent to the intervention protocol.

Below is a flow diagram (Figure 1) of the progress through the phases of a randomized trial of three groups (that is, enrolment, intervention allocation, follow-up, and data analysis).

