Missing data: Analyses will follow an intention-to-treat principle. Missing outcome data will be described (extent, pattern, and reasons when available). The primary repeated-measures models will be implemented using estimation procedures that allow inclusion of participants with incomplete follow-up (under a missing-at-random assumption). If missingness exceeds a minimal threshold or appears differential by group, sensitivity analyses will be performed (e.g., multiple imputation and/or complete-case/per-protocol comparisons).

All analyses will be performed in SPSS (Version 21, Chicago, IL, USA), with the significance threshold set at α = 0.05.

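### None of the missing-data sensitivity analyses given as examples is a controlled departure from the missing-at-random assumption of the primary FES-I model

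*Protocol article*

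**What the plan says.** All of the missing-data plan is in section 2.17 of the protocol article.

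- Principle: "Analyses will follow an intention-to-treat principle".
- Primary model: repeated measures, using "estimation procedures that allow inclusion of participants with incomplete follow-up (under a missing-at-random assumption").
- Trigger for further work: "If missingness exceeds a minimal threshold or appears differential by group". No number is attached to the threshold.
- What then follows: "sensitivity analyses will be performed (e.g., multiple imputation and/or complete-case/per-protocol comparisons").

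Three other places bear on it.

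- Section 2.9 gives the only adherence rule: "Participants who complete at least 80% of the planned sessions will be considered adherent to the intervention protocol".
- Section 2.1, describing the semi-squat arm, says "Interventions will occur twice weekly, for a total of 10 sessions"; the seated arm gets the same vibration parameters. Section 2.9 says that control participants "will only undergo the scheduled clinical, sociodemographic, and outcome assessments" alongside their routine activities.
- Section 2.16 allows for up to 20% loss to follow-up. Sections 2.1 and 2.11 give FES-I one baseline and one post-intervention measurement.

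**The concern.** A sensitivity analysis for missing data is useful if it shows how the conclusion moves when the primary assumption is wrong by a stated amount. Here that assumption is that, given baseline FES-I and group, people without a post-intervention score would have scored like those who have one.

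There is reason to doubt it in this trial. Only Groups B and C carry ten extra laboratory sessions, participants are asked about discomfort, pain and fatigue at each one (section 2.7), they cannot be fully blinded (section 2.6), and the primary outcome is self-reported. Loss linked to discomfort or lack of benefit is plausible in the SVT arms and has no counterpart in Group A.

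If that happens and only the named checks are run, a reader could be told that the result is robust although the assumption in doubt was never varied. The open trigger and the and/or wording also leave the decision to run a check, and the choice of check, until the data are in view.

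**Working it through.** **Scale.** Section 2.16 uses f = 0.25, α = 0.05, power 0.80 and three groups. A one-way ANOVA with noncentrality f² × N gives power 0.8049 at N = 159, so the stated 159 (53 per group) is reproduced. If both SVT arms differ from control by d SD, the group means are 0, d, d, and f = d × √(2/9) = 0.471d. So f = 0.25 means d = 0.25/0.471 = 0.53 SD.

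**Each named check in turn.**

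1. *Multiple imputation.* A participant lost to follow-up has a baseline FES-I and nothing else on that scale. Imputing the post score from baseline within group uses the information the primary model uses, under the same assumption.
2. *Complete-case.* A Group × Time test on completers compares mean change scores among completers. It ignores the baselines of those lost, so it is biased when loss depends on baseline, where the primary model is not.
3. *Per-protocol.* The adherence rule gives 0.80 × 10 = 8 sessions. Group A has no study sessions, so on this rule nobody in A can be excluded.

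**Simulation.** Assumptions, none from the documents: true effect zero; 20% drop-out in an SVT arm; ignorable drop-out in control; logistic slope 1.5 per SD of the driver; a further 15% excluded for non-adherence in the SVT arm only, with the same driver; pre-post correlation 0.5 to 0.8. Entries are bias in SD units across that range of correlation; negative means a false benefit of SVT.

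| Drop-out depends on | Primary model and imputation | Complete-case | Per-protocol |
|---|---|---|---|
| baseline score (missing at random) | 0.00 | +0.05 to +0.11 | +0.07 to +0.17 |
| post score | −0.18 to −0.09 | −0.11 to −0.05 | −0.17 to −0.07 |
| change | −0.18 to −0.13 | −0.23 to −0.14 | −0.34 to −0.21 |
| stable underlying level | −0.09 to −0.05 | 0.00 | 0.00 |

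A run at trial size (64 per arm, correlation 0.6, drop-out 10% in control and 20% in SVT, related to the post score; Monte Carlo error about 0.006) gave −0.151 for the primary model, −0.151 for imputation, −0.085 for complete-case and −0.116 for per-protocol.

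In rows 2 and 3 every analysis errs in the same direction, so broad agreement would give no warning. In row 1 the primary result is right and two checks disagree with it. Neither agreement nor disagreement therefore tells the reader whether drop-out drives the result.

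**Hand illustration.** Assume that 20% of an SVT arm is missing with baselines like the rest, that completers benefit by 0.50 SD and that non-completers benefit by 0. The effect in everyone randomised is 0.8 × 0.50 + 0.2 × 0 = 0.40 SD. The primary model, imputation and complete-case all return about 0.50, and 0.50/0.40 = 1.25. With 10% missing it is 0.50 against 0.9 × 0.50 = 0.45.

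**What a controlled departure shows.** Shifting imputed values by δ in an arm with share m missing moves that arm's mean by m × δ. At m = 0.20, shifts of 0.25, 0.5 and 1.0 SD move it by 0.05, 0.10 and 0.20 SD; at m = 0.10, by 0.025, 0.05 and 0.10 SD. Imputing the SVT non-completers from control in the hand illustration returns about 0.40.

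**The case against.** The strongest reply is that the list is introduced by e.g. in a condensed journal article, and that delta-adjusted or control-based models are detail that an analysis plan would hold. That stands as far as it goes: a reader might infer that the trial will run no analysis outside missing at random, and the article does not establish this. The point is confined to the checks the article chose to name.

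Other stronger readings also fail.

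- *That the checks run only above a threshold.* Section 2.17 also triggers them when missingness appears to differ by group, which covers excess loss in the SVT arms. It promises to describe the pattern of missingness and the reasons where known, and section 2.9 logs reasons for missed sessions. Loss that is similar across arms but informative in B and C could still escape the trigger if it stays under the undefined threshold.
- *That every check rests on the same or a stronger assumption.* Complete-case analysis of change is unbiased when drop-out depends only on a stable underlying level, where the primary model is not. Imputation with auxiliary variables could relax the assumption somewhat, though none are named.
- *That agreement is built in.* This holds only for imputation against the primary model; −0.151 against −0.085 shows that complete-case can diverge.
- *That per-protocol favours SVT.* The table shows biases of either sign.
- *That per-protocol can be defined only in B and C.* No per-protocol set is defined. A broader definition, for example one using assessment timing, could exclude controls. The statement here is conditional on the 80% rule.
- *That missing sessions means a missing outcome.* Under intention to treat, a participant who stops sessions can still give a post-intervention FES-I. The 20% is a planning margin for loss across the trial, not a forecast for the SVT arms.

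**Conclusion.** The point holds in limited form. The primary model is valid "under a missing-at-random assumption", and none of the three analyses named as examples departs from that assumption by a stated, adjustable amount. Imputation on the same two FES-I values repeats it. Complete-case swaps it for a different, usually stronger one. Per-protocol on the 80% rule compares selected SVT participants with unselected controls, so it breaks the randomised comparison and answers a question about adherence.

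The size is conditional. With 20% drop-out in an SVT arm related to the post score or to change, the assumed models give a false benefit of 0.09 to 0.18 SD in the primary estimate, against the 0.53 SD that the sample size implies if both SVT arms are equal. The 0.50 against 0.40 SD comparison rests wholly on its chosen inputs. With little or ignorable loss the bias would be small or nil. The primary analysis need not change; what is lacking is a check that tests its assumption. This is an inexpensive improvement, not a fault that invalidates the plan.

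**What to change.** In section 2.17, or in the analysis plan if it does not already do so:

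1. Pre-specify for FES-I at least one missing-not-at-random sensitivity analysis, run whenever any post-intervention FES-I value is missing, with no threshold. Suitable choices are multiple imputation with a delta shift applied in B and C and raised until the conclusion changes (tipping point), and/or imputation of B and C non-completers from Group A.
2. Label the per-protocol comparison as a descriptive adherence analysis, define its population, and take it off the list of missing-data checks.

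Multiple imputation and complete-case analyses may stay as supplementary results, with a sentence saying which assumption each makes.

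Cost: about two sentences and a few hours of analysis, some of it outside the standard menus of SPSS, the stated software. Sensitivity estimates may be less favourable to SVT. Design, sample size and conduct are unaffected.
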